## Storage

The product is stored at 2-8°C (36-46°F).

## Drug Accountability

Protalix will provide drug accountability forms to assist the investigator in maintaining current and accurate inventory records covering receipt, dispensing, and the return of investigational drug supplies. When a shipment is received, the investigator or pharmacist will verify the quantities received and return the acknowledgment to the study monitor or designee. The investigational drug accountability record includes the study identification of the person to whom the drug is dispensed, the quantity and the date of dispensing and any returned or unused drug. This record is in addition to any drug accountability information recorded on the Case Report Form (CRF). These records will be readily available for inspection by a monitor or Protalix audits and are open to regulatory authority inspection at any time.

When the supplies are returned to Protalix, the investigator or Phase I unit site manger signs the investigational drug return log to verify that all unused or partially used supplies have been returned and that no study supplies remain in the investigator’s possession. One copy of all inventory records and the return statement are retained by the investigator for the study files.

At study termination, unless otherwise specified, all unused drug supplies including partially used containers and the study drug accountability log should be returned to Protalix, Ltd.

## Overdosages

No over-dosage to currently approved human glucocerebrosidase have been reported with either the placental derived or the recombinant glucocerebrosidase enzymes

# ADVERSE EVENTS

An adverse event is an undesirable or unintentional event that occurs during the usage of the study drug, whether or not it is related to the drug; this includes clinically significant changes in laboratory values. Regardless of the severity or relationship to the investigational drug, all adverse events occurring during the study period are to be recorded in the subject's CRFs. The phrase "associated with the use of the drug" is defined as a reasonable possibility that the event may have been caused by the drug under investigation.

## Definitions of Severity and Relationship to Study Medication

### Relationship to Study Medication

The following definitions should be used to assess the relationship between an adverse event and the study drug.

Unrelated: The event is clearly related to other factors, such as a subject's clinical state, therapeutic interventions or concomitant medications.

Remotely Related: The event was most likely produced by other factors, such as a subject's clinical state, therapeutic interventions or concomitant medications, and does not follow a known response pattern to the study drug.

Possibly Related: The event has a reasonable temporal relationship to the study drug administration and follows a known response pattern to the study drug. However, a potential alternate etiology may be responsible for the event. The effect of drug withdrawal is unclear. Rechallenge information is unclear or lacking.

Probably Related: The event follows a reasonable temporal sequence from the time of drug administration, and follows a known response pattern to the study drug and cannot be reasonably explained by other factors. There is a reasonable response to withdrawal of the drug. Rechallenge information is not available or advisable.

Related: The event follows a temporal sequence from the time of drug administration and follows a known response pattern to the study drug. It either occurs immediately following the study drug administration, improves on stopping the drug, or reappears on repeat exposure.

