## Rationale

Human glucocerebrosidase has been used successfully for the clinical treatment of Gaucher disease for several years from both natural and recombinant sources (CHO production platform). This is the first trial to utilize a recombinant active form of lysosomal enzyme, glucocerebrosidase, (human prGCD) which is expressed and purified in a bioreactor system from transformed carrot plant root cell line.

Since the glycosylation pattern of recombinant human glucocerebrosidase must possess high mannose structures to increase uptake in target cells, the expression of human glucocerebrosidase in plant cells could be of great value. As mentioned above several approaches are utilized to control and tailor protein glycosylation in plants (Dwek RA *et al*. 2002). Protalix’s approach attempts to localize the expression to a specific compartment in the cell. For example, retaining the protein in the endoplasmic reticulum (ER) prevents plant specific modification from being carried out in the Golgi (Neuhaus JM and Rogers JC 1998; Vitale A and Galili G 2001). This approach has been adopted in developing active human prGCD.

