### Safety Assessments

Safety parameters at each follow-up assessment, as well as changes from baseline, will be examined and summarized for descriptive purposes. Safety will also be assessed through the recording of adverse events. Adverse events will be classified by body system using the MedDRA classification, and tabulated based on the incidence, severity, and causality to study treatment.

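### The causality scale in Section 7.1.1 has no category for a well-timed novel reaction without a likely other cause

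*Protocol*

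**What the plan says.** Section 7.1.1 gives five definitions, to be used for every assessment of the relationship between an adverse event and the study drug.

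- Unrelated: other factors are clearly the cause.
- Remotely Related: "The event was most likely produced by other factors", with the further condition "and does not follow a known response pattern to the study drug". Both parts must hold.
- Possibly Related requires timing and pattern together: "The event has a reasonable temporal relationship to the study drug administration and follows a known response pattern to the study drug". An alternative cause may still be responsible.
- Probably Related: reasonable timing, "and follows a known response pattern to the study drug and cannot be reasonably explained by other factors".
- Related: "The event follows a temporal sequence from the time of drug administration and follows a known response pattern to the study drug". In addition, the event must be immediate, improve when the drug is stopped, or return on re-exposure.

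The Rationale (Section 1.1) states: "This is the first trial to utilize a recombinant active form of lysosomal enzyme, glucocerebrosidase, (human prGCD"). Section 1.2 reports no obvious treatment-related reactions in the mouse study or, as a preliminary result, in the marmoset study.

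The introduction to Section 7 words causality differently. There, an association with the drug "is defined as a reasonable possibility that the event may have been caused by the drug under investigation". Under Section 9.4.2, adverse events are "tabulated based on the incidence, severity, and causality to study treatment". The synopsis says the same.

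**The concern.** A first trial of a product should be able to record a reaction that nobody has seen before and say whether the drug plausibly caused it. Here the three upper categories all presuppose that the reaction type is already known for this drug, and the two lower categories presuppose another cause. An event of the kind the study most needs to detect may therefore have nowhere to go.

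Safety is the primary objective, and causality is one of the three axes on which adverse events are tabulated. The investigator assigns the rating and enters it on the CRF during the study. A later analysis document cannot repair ratings collected under a scale with a gap; they would have to be re-adjudicated.

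**Working it through.** No arithmetic applies, and the protocol states no figure on this point. The check treats the five definitions as logical conditions and applies them to one type of event: plausible timing, with no response pattern known for prGCD. The only thing varied is how strong the alternative explanation is.

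| Alternative explanation | Unrelated | Remotely Related | Possibly | Probably | Related | Result |
| --- | --- | --- | --- | --- | --- | --- |
| Clearly the cause | met | – | fails: pattern | fails: pattern | fails: pattern | Unrelated |
| Most likely the cause | fails | met | fails: pattern | fails: pattern | fails: pattern | Remotely Related |
| Possible, not most likely | fails | fails: not most likely | fails: pattern | fails: pattern | fails: pattern | no category |
| None reasonable | fails | fails: no other factor | fails: pattern | fails: pattern | fails: pattern | no category |

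The last two rows are the gap. Three points confirm it.

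1. The pattern condition is required, not supportive. In Possibly, Probably and Related it is joined to the timing condition by *and* ("The event has a reasonable temporal relationship to the study drug administration and follows a known response pattern to the study drug", "and follows a known response pattern to the study drug and cannot be reasonably explained by other factors", "The event follows a temporal sequence from the time of drug administration and follows a known response pattern to the study drug").
2. Re-exposure does not rescue the event. Each subject receives prGCD on Days 8, 15 and 22, so a reaction on Day 8 could return on Day 15. Return on re-exposure counts towards Related only in addition to the pattern condition, not in place of it.
3. The protocol gives the pattern condition no content for this drug. It describes no prGCD reaction pattern. The human experience in Sections 1, 1.1, 3.5 and 6.8 is with other glucocerebrosidase preparations.

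The wording in the introduction to Section 7 gives a different answer. A well-timed event with no other reasonable cause would readily meet a test of reasonable possibility, which asks for no known pattern. The same event has no rating under Section 7.1.1.

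**The case against.** **A pattern may be available from elsewhere.** Section 1 cites about 14 years of enzyme replacement in over 3000 patients, Section 3.5 says the two higher doses were used before with other preparations, and the protocol refers to an Investigator's Brochure that is not shown here. Investigators could borrow a pattern from those sources, or let one build up over repeated infusions. This stands in part: it would be too strong to say that no pattern can be known. But the definitions refer to the study drug, and borrowed experience does not cover reactions new to the plant-cell product.

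**Other safety information is untouched.** This stands. All adverse events are recorded whatever their relationship, serious events are reported whatever their cause, and events are also tabulated by incidence and severity. With six subjects who each receive vehicle first, a cluster of reactions would still be visible.

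**Section 7's other wording is not a rival scale.** It defines a phrase that the protocol does not use again. This also stands: it shows a lack of alignment rather than two competing grading rules.

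**A reader might infer that the table is biased towards not related,** with every novel reaction counted as unrelated. The documents do not support this. The literal result is an event with no category, and how an investigator would force a choice is not stated.

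**A reader might also infer that the stopping and withdrawal criteria are disabled.** That goes too far. Sections 3.6 and 8 rest on the judgment of named roles, and Section 8 also allows withdrawal in the subject's interest without a causality test. Section 3.6 uses a term, definitely related, that is not on the scale, and points to Section 7.2 rather than 7.1.1.

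**Conclusion.** The concern holds in limited form. As written, Section 7.1.1 cannot classify a well-timed reaction that is new to prGCD and has no clear or most likely other cause. Of the four cases examined, two have no category, and none can reach Possibly or higher. The harm is confined to the causality axis of the adverse event tabulation, which becomes unreliable for these events because ratings will be missing or will depend on how each assessor departs from the definitions.

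No numerical size can be given. The protocol gives no expected number of reactions and no rule for events that fit no category, so any count of misrated events would be invented.

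The conclusion assumes that the definitions are applied as worded, and that at least some possible reactions lie outside anything already described for related enzymes or in the Brochure. If investigators use free judgment instead, the gap may be filled in practice, but the definitions then no longer make ratings consistent.

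**What to change.** Before first dosing, change Section 7.1.1 and the matching CRF field:

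- Make a known response pattern a supportive criterion for Possibly, Probably and Related, no longer a required one.
- Remove the absence of a known pattern as a condition of Remotely Related.
- Define the categories by timing, alternative cause, and response to stopping and to re-exposure, so that every event fits exactly one.
- Add to Related an explicit condition that other factors do not reasonably explain the event. Without it, deleting the pattern condition would let an event qualify on immediate timing alone.
- Align the scale with the reasonable-possibility wording in the introduction to Section 7.
- Reconcile the terms definitely related (Section 3.6) and probably related (Section 8) with the categories of the scale. What those clinical rules should be is for the sponsor and investigator.

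The cost is protocol and CRF wording. The downside is that a few more events may be counted as related. If the change waits until dosing has begun, ratings already given would need re-adjudication.

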### Severity

Mild Adverse Events:

A mild adverse event is one where the symptoms are barely noticeable to the subject. It does not influence performance or prevent the subject from carrying on with normal life activities.

Moderate Adverse Events:

A moderate adverse event is one where the symptoms make a subject uncomfortable and cause some impairment to normal life activities. Treatment for symptom(s) may be required.

Severe Adverse Events:

A severe adverse event is one where the symptoms cause severe discomfort to the subject and severely limit the subject's normal daily activities. Treatment for symptom(s) is given. Note that serious and severe are not synonymous. A serious adverse event must fulfill the requirements listed in the definition below.

The Common Toxicity Criteria will be used for grading the severity of each AE (Appendix 2)

## Serious Adverse Event Reporting

A serious adverse event (SAE) is any event that suggests a significant hazard, contraindication, side effect, or precaution. An SAE is defined as any untoward medical occurrence that at any dose:

- - - Results in death
    - Is life-threatening
    - Requires hospitalization or prolongation of existing hospitalization
    - Results in persistent or significant disability or incapacity
    - Is a congenital anomaly, cancer, overdose or birth defect

Life Threatening is defined as an event where a subject is at risk of death at the time of the event. It does not refer to an event that hypothetically might have caused death if it was more severe. Disability is defined as a substantial disruption of a person's ability to conduct normal life functions. An unexpected adverse event is one that has not been previously observed, or one that is of a specificity or severity not consistent with the current investigator brochure.

Any serious adverse event should be reported to the Sponsor's Monitor by telephone or fax within 24 hours of the event. The call should be followed-up with a written report within five days. Full details of the event, any sequels and an assessment of the relationship to the study drug, must be provided in the report. Any serious adverse events must also be reported to the Institutional Review Board (IRB) within 48 hours and a copy of this report must be sent to the Sponsor's Monitor. Cases of death must be reported immediately to the Hospital Director. Protalix will notify the appropriate regulatory authorities as required.

In the event of an SAE, the Medical Director must be contacted immediately by calling the following telephone # within 24 hours of disclosure of the incident:

[contact]; [name]

All SAEs must be reported to the IRB. The investigator will promptly supply all information identified and requested by the sponsor and its contracted monitor regarding the SAE.

## Documentation of Adverse Events

All adverse events must be recorded in the CRFs. When an adverse event occurs, the following information and assessments should be recorded in the adverse event section of the CRF:

1. The symptoms, signs, abnormal laboratory finding or a diagnosis of the event.
2. The date and time of onset of the event, using the 24 hour clock, where midnight is 00:00 and noon is 12:00.
3. The adverse event severity, using the criteria outlined above.
4. The relationship of the event to the study drug as outlined above.
5. The description of any action taken regarding study drug disposition.
6. Any required therapy, medication, treatment or diagnostic procedure.

Follow-up of a subject should be conducted until resolution of the adverse event.

The investigator is responsible for the appropriate medical management of all adverse events.

The condition of each study subject will be monitored throughout the study by the treatment clinician or designee. At each visit, symptoms and signs will be observed by the treatment clinician (or designee) or volunteered by the subject. In addition, signs and symptoms that may have occurred since the previous visit will be elicited by asking open or indirect questions, such as “How have you felt since your last visit?”

All AEs, whether observed by the examination clinician, elicited from or volunteered by the subject, will be recorded on the CRF. Data will include start and end dates, investigator-specified severity and relationship to study medication, and action taken with respect to the study medication. Whether the event resulted in death, required (or prolonged) hospitalization resulted in persistent or significant disability/incapacity, required intervention to prevent any of those outcomes, and/or was reported to the sponsor as serious will also be recorded.

## Current and Concomitant Medications

The name and duration of treatment of all medications taken at the time of the inclusion or during the study will be recorded on the CRF. Dosage, route of administration and indication will also be specified.

# SUBJECT WITHDRAWAL

Subjects will be discontinued from the study prematurely if:

1. An intercurrent illness occurs which precludes further treatment.
2. A serious adverse event occurs, which in the judgment of the principle investigator, managing physicians, and/or sponsor, is probably related to the study drug and cannot be acceptably managed.
3. The subject requests to be withdrawn from the study.
4. The principal investigator decides that it is in the subject's best interest.
5. The subject is noncompliant with the protocol.
6. The sponsor decides to discontinue the study.
7. Subjects who participates in another investigational drug trial

All subjects prematurely discontinued from the trial, regardless of cause, will have follow up visits according to the study schedule, for safety. The reason(s) for withdrawal will be recorded in the CRF by the investigator and the occurrence reported to the medical monitor.

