**PROTOCOL SYNOPSIS**

**Protocol Number:** P-01-2005

**Title:** A Phase I, Non-Randomized, Open Label, Single Dose, Dose-Escalation Safety Study of Recombinant Human Glucocerebrosidase (prGCD) in Healthy Volunteers

**Study Phase:** 1

**Study Site:** Jerusalem Phase I unit, Hadassah Medical Organization, Jerusalem, Israel

**Test Material:** human prGCD 15 units/kg; 30 units/kg; 60 units/kg and vehicle

**Dose:** human prGCD will be administered as an intravenous infusion (IV) delivered over 1.5 hour. The rate of infusion is to be 135 mL/1.5 hr (1.5ml/minute). The infusion rate will be the same over 90 minutes for all doses. All subjects will receive all doses in a sequential manner starting with vehicle. Subjects will be closely monitored for 2 hours from the time of the initiation of the infusion.

Vehicle will be given at the baseline visit. The initial human prGCD dose of 15 units/kg will be given at Day 8; 30 units/kg dose will be administered on Day 15, and 60 units/kg dose on Day 22.

**Route of Administration:** Intravenous (IV)

**Controls:** Each subject will receive vehicle and thereby will be his/hers own control.

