The Principle Investigator will review all test results and AE report 24h prior to escalation to the next dose level. The dose will be increased based on review of drug toxicity by the Principle Investigator and the Medical Director of Protalix Ltd. A follow up safety visit will take place at Day 29.

Plasma levels of human prGCD will provide a pharmacokinetic profile, including AUC0-inf, Tmax, Cmax and Cmin and will be calculated for each subject.

All PK samples of human prGCD will be analyzed at the end of the study for all subjects. This data will be used as adjunct information for a safety review, which will include a review of adverse events, changes in vital signs, physical examination and clinical laboratory test results. Unexpectedly high plasma concentrations will be reviewed for correlation to related adverse events.

This study is conducted according to FDA and European GCP guidelines.

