## Stopping Criteria

If any subject experiences a serious adverse event, that in the judgment of the Principle Investigators and/or the Medical Director of Protalix Ltd. is life-threatening and definitely related to study medication (see Section 7.2), the study will be stopped

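### Section 8 item 2 makes withdrawal after a drug-related SAE mandatory only if the event is also unmanageable, so a healthy volunteer's next, doubled dose is left to discretion

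*Protocol*

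**What the plan says.** Five parts of the protocol bear on whether a subject who has had an SAE is dosed again.

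- **Withdrawal (Section 8, item 2).** A subject is taken off the study for an SAE that, in the judgment of the investigator, managing physicians and/or sponsor, "is probably related to the study drug and cannot be acceptably managed". Both conditions must hold.
- **Other withdrawal grounds (Section 8).** Item 4 reads "The principal investigator decides that it is in the subject's best interest" and item 6 reads "The sponsor decides to discontinue the study". The remaining items concern intercurrent illness, the subject's own request, noncompliance and joining another trial.
- **Stopping rule (Section 3.6).** It applies to an SAE that in the judgment of the investigators and/or the Medical Director "is life-threatening and definitely related to study medication (see Section 7.2), the study will be stopped".
- **Escalation (Synopsis and Section 3).** "All subjects will receive all doses in a sequential manner starting with vehicle". Section 3 adds: "The dose will be increased based on review of drug toxicity by the Principle Investigator" together with the sponsor's Medical Director. No toxicity grade or event is named that would block the increase.
- **What counts as serious (Section 7.2).** The list goes beyond death and threat to life. One entry is "Requires hospitalization or prolongation of existing hospitalization".

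**The concern.** Item 2 is the only rule written for an individual subject who has had an SAE. Its second condition turns on whether the event could be handled, not on whether the subject should be exposed again. An event can be serious, attributed to the drug and well treated, and the mandatory rule then does not apply.

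That threshold is loose for this population. The volunteers are healthy and have no disease for the enzyme to treat, so no therapeutic benefit offsets the risk of a second reaction. Section 1.1 calls this the first trial of the enzyme made in carrot cells. Because escalation is within subject, continuing after such an event means re-exposing the same person to a higher dose about a week later.

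**Working it through.** No statistical figure in the plan is at issue, so the check is to apply each rule to one defined case.

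**Test case.** After 15 or 30 units/kg, a subject has an SAE that is serious because of hospitalization. It is graded Probably Related or Related, is not life-threatening, resolves with treatment and is judged acceptably managed.

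| Rule | Condition | Does it bind here? |
| --- | --- | --- |
| Section 8 item 2 | SAE probably related and not acceptably manageable | No: second condition fails |
| Section 3.6 | SAE life-threatening and definitely related | No: first condition fails |
| Section 8 item 1 | Intercurrent illness that rules out further treatment | No: the event is attributed to the drug |
| Section 8 items 4 and 6 | Investigator's or sponsor's decision | Only if that decision is taken |
| Section 8 items 3, 5 and 7 | Subject's request, noncompliance, other trial | Not triggered by the event |
| Section 3 review | Toxicity review before each increase | Review required, outcome not fixed |
| Section 6.2 | Infusion may be slowed after an adverse effect | Optional, and does not withhold the dose |

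No row requires dosing to end.

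**Two neighbouring cases.**

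- A life-threatening SAE graded only Probably Related and treated successfully also falls outside both SAE rules. This assumes that definitely related in Section 3.6 means the top grade of Section 7.1.1, which is called simply Related.
- An SAE graded Possibly Related falls outside item 2 whether or not it can be managed.

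**Dose steps affected.** Doses are from the Synopsis: 15, 30 and 60 units/kg on Days 8, 15 and 22.

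- 30 / 15 = 2 and 60 / 30 = 2, so each step is a doubling, nominally 7 days after the last dose.
- The step from vehicle to 15 units/kg is not a doubling, and no dose follows 60 units/kg. Two steps per subject are therefore concerned.

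**Cost of a binding rule.** Six subjects with three active doses each give 6 × 3 = 18 planned active infusions.

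- Withdrawal after 15 units/kg loses 2 infusions: 2 / 18 = 11.1%.
- Withdrawal after 30 units/kg loses 1 infusion: 1 / 18 = 5.6%.
- With k subjects withdrawn at either point, 6 − k reach 60 units/kg: 5 for one, 4 for two.

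**The case against.** The best answer is that nobody is re-dosed by default. Each increase depends on a review by two parties, and Section 7.2 requires the Medical Director to be told promptly of any SAE. Item 4 is binding once the investigator has decided. The manageability clause is itself a judgment, which could be read to include whether the event would be manageable on further dosing. A careful investigator would very probably withhold the dose. All of this stands, and it limits the weight of the point. It does not supply a rule: none of these provisions names an event after which the next dose may not be given.

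Three stronger readings are tempting, and the documents do not support them.

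- **That any SAE treated with success counts as acceptably managed.** The phrase is undefined and the assessors may decide otherwise. The gap exists only where they judge the event acceptably managed.
- **That item 2 contradicts the protocol on rechallenge.** The definition of Probably Related in Section 7.1.1 says "Rechallenge information is not available or advisable", and a reader might infer a ban on re-exposure. The sentence describes the evidence behind a causality grade. It gives no dosing instruction, so there is no conflict.
- **That the option to slow the infusion shows harm or protection.** Slowing is optional and starts when an effect appears, so the resulting duration is not fixed. Nothing here rests on it.

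It is also fair to object that a rule limited to the two highest grades would leave much of the gap open. That is accepted, and it is why the recommended wording includes Possibly Related. One limit remains. The definitions of all three grades refer to a known response pattern, which a product in its first trial may not yet have. A novel reaction could therefore still depend on the review and item 4.

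**Conclusion.** The point holds as a rule set too loosely, not as an error or a contradiction. For a drug-related SAE that is judged acceptably managed, and that is not both life-threatening and definitely related, only discretion stands between a healthy volunteer and a doubled dose.

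The conclusion assumes that item 2 is read as written, with both conditions required, and that probably related in item 2 includes the higher Related grade. If it does not, the mandatory rule is narrower still. The protocol gives no SAE rate, so nothing is claimed about how likely the case is. Because a two-party review precedes every increase, this is a cheap improvement to subject protection. It does not show that the trial as planned is unsafe.

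**What to change.** Replace Section 8 item 2 with wording to this effect: *Any serious adverse event that the principal investigator, managing physicians and/or sponsor judge to be Possibly Related, Probably Related or Related under Section 7.1.1; the subject then receives no more study drug.* This removes the manageability clause and ties the rule to grades the protocol already defines. At minimum, delete that clause and name the Probably Related and Related grades. Leave the Section 3 review, item 4 and the safety follow-up of withdrawn subjects as they are. Severe reactions that are not serious stay with the review and item 4.

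The change is one sentence and uses the existing assessors. Its price is the loss of infusions shown above for each subject withdrawn, and thinner safety and pharmacokinetic data at 60 units/kg. Section 9.4.4 makes no power calculation and calls the analyses exploratory and descriptive, so no inferential claim is weakened. Section 8 keeps withdrawn subjects in scheduled safety follow-up. One further cost is that Section 7.2 lists overdose as an SAE criterion. A trivial event that is serious only on that ground would also end dosing if it were graded as related.
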